### Trial organization

The Cleveland Clinic Department of Outcomes Research is the coordinating center for this trial and is responsible for the central randomization, trial database, data consistency checks, data analyses, and coordination of participating centers worldwide.

The group responsible for trial steering included the primary investigator from three of the research sites, a statistician from the coordinating center, two wound care nursing specialists from two of the research sites, and the chairmen of the Departments of Research from three of the research sites.

The endpoint adjudication committee members included the coordinating center PI, the statistician, and the chairman of the coordinating center research department.

The data management team included a statistician, a member of the database and data quality control arm of the coordinating center research department, and a research fellow. Day-to-day trial conduct is undertaken by research personnel to include fellows and nurses, the primary investigator from each site, two wound care nurses from the coordinating center, the database manager (weekly), and the statistician (weekly).

No stakeholder or public involvement group was utilized for the design of this trial.

## Adverse event reporting

### Reporting, recording, and follow-up of adverse events

The investigator will assess the relationship between protocol treatment and the occurrence of AEs, and this assessment will be recorded in the database for adverse events. The key potential adverse events of interest are restricted to skin irritation/allergies, and these skin manifestations will be scored with the International Common Terminology Criteria for Adverse Events (CTCAE), version 5.0, for adverse event reporting. Due to the non-systemic nature of the intervention, and the complexity of inpatient care and number of concurrent therapies being administered to this population, no other adverse events will be collected or reported. The investigator will follow each adverse event of interest until the event has resolved to baseline grade or better or is assessed as stable by the investigator or until the patient is discharged from hospital. During the study period, resolution of adverse events (with dates) should be documented on the adverse event electronic case report form (eCRF) and the patient’s medical record to facilitate source data verification. If, after follow-up, return to baseline status or stabilization cannot be established, an explanation should be recorded on the adverse event eCRF. No renumeration or compensation is provided to participants.

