### Trial population

We will include a minimum of 548 adult inpatients who meet the following criteria: (1) hospital inpatients, (2) new or established stage 1–2 sacral/ischial pressure injuries, (3) provide written informed consent in English. Consent is given by the patient or their legally authorized representative (LAR). Subjects enrolled via LAR will be themselves consented when able. Consent will be done in person or by telephone by investigators.

Patients with a pacemaker/AICD, active rhabdomyolysis, gluteal skin breakdown, and unstable fractures at risk of displacement by IES will be excluded. Patients with BMI > 40 kg/m^2^ will also be excluded based on concerns about not being able to elicit a reliable contraction of the muscle with the device. Patients with atrial or ventricular wires after cardiac surgery can be enrolled so long as they are not being actively paced or, in the opinion of the treating physician, likely to requiring pacing during the trial. Patients with multiple pressure injuries in higher stages can be enrolled as long as one of the sacral or ischial injuries is stage 1 or 2.

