#### Exploratory endpoints

We will assess cost effectiveness of IES vs standard care within a subset of the patients studied. We will measure incremental cost-effectiveness ratios (ICERS) between traditional care and IES interventions in the treatment of pressure ulcers. Safety assessment is as follows: results from each of the 5 possible side effects listed on Patient and Assessor Questionnaire will be summarized as (1) proportion of patients ever having the event across their follow-ups, (2) severity grade across follow-ups for those having the event, and (3) severity grade for all patients, assigning a 0 to those without the event. Severity grade will be summarized using median [quartiles] and mean (SD). Confidence intervals within and between randomized groups will be estimated using bootstrap resampling with replacement to account for within-subject correlation across measurements.

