### Interim analysis

Interim analyses will be performed at each 25% of the planned enrollment using a group sequential design assessing the treatment effect on the primary outcome for efficacy and futility. We will use a gamma spending function with gamma parameters − 4 for efficacy and − 1 for futility. Stopping boundaries will be statistically non-binding; statistical accommodation for this option was made in the sample size calculations. The decision whether to stop a study at any interim analysis would be made by the DSMB, which would consider not only the statistical boundaries but other information as well. For example, if a futility or efficacy boundary was crossed at the first look, the DSMB might consider continuing the trial to obtain a more precise estimate of the treatment effect.

All data and results will be submitted to the data and safety monitoring board (DSMB) for review on an A versus B basis unless the DSMB requests to be unblinded. The DSMB is made up of physicians from multiple trial sites and a statistician (Additional file 5). The committee will assess any possible safety concerns, efficacy, and futility and advise if discontinuation is warranted and will meet at least yearly. DSMB members are independent from the sponsor and report to and communicate with the IRB and the steering committee.

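### Adverse event collection is limited to skin reactions with no exception for serious device-attributed events, although the plan itself foresees a non-skin device harm and gives the DSMB a general safety remit

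*Protocol article*

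**What the plan says.** The protocol article, under Reporting, recording, and follow-up of adverse events, has the investigator judge the relation of adverse events to treatment. It then narrows what counts: "The key potential adverse events of interest are restricted to skin irritation/allergies", graded by CTCAE version 5.0. Everything else is ruled out: "no other adverse events will be collected or reported". Two reasons are given. The first begins "Due to the non-systemic nature of the intervention". The second is that these inpatients are complex and receive many therapies at once.

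Three other places bear on the rule:

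- **Trial population:** "Patients with a pacemaker/AICD, active rhabdomyolysis, gluteal skin breakdown, and unstable fractures at risk of displacement by IES will be excluded". Patients with temporary cardiac wires after surgery may enter only if they are not being actively paced and the treating physician does not think pacing likely during the trial.
- **Interim analysis:** "The committee will assess any possible safety concerns, efficacy, and futility". The board works from the data and results submitted to it, and it may advise stopping.
- **Exploratory endpoints:** the safety assessment summarises "results from each of the 5 possible side effects listed on Patient and Assessor Questionnaire".

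**The concern.** The article does more than leave the handling of serious events to a fuller document. It states that they will not be collected unless they are skin events. The investigator's causality judgement therefore covers skin events only. If a participant had a displaced fracture, muscle injury or rhythm disturbance, and the investigator blamed the device, the rule as worded would keep it out of the adverse event data.

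Two things are at stake. The DSMB cannot weigh events that were never recorded, although its remit is not limited to skin. The trial report also could not say anything about non-skin device harm, because an absence of recorded events would only reflect the collection rule. This matters more because the Background describes earlier clinical trials of the device as limited to phase I.

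**Working it through.** No arithmetic applies. The check sets the sections of the protocol article side by side.

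1. **Is the restriction explicit?** Yes. The adverse event section gives the scope, the exclusion of all else, and reasons. It states no exception for seriousness or for attribution to the device.

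2. **Does the plan foresee non-skin device harm?** For one hazard, expressly: Trial population excludes unstable fractures because stimulation might displace them. For pacemaker/AICD and active rhabdomyolysis no reason is given. A cardiac-device or muscle concern is a natural inference, as it is for the condition on pacing wires, but it remains an inference. The BMI exclusion shows that a criterion can rest on device performance instead.

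3. **Do the stated reasons support the rule?** The non-systemic argument does not reach a local mechanical harm such as fracture displacement. The complexity argument supports not collecting every inpatient event. It does not support leaving out a serious event that an investigator has attributed to the device.

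4. **Could another data stream capture such an event?**

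| Source in the article | What it gives the DSMB | Non-fatal serious non-skin device harm? |
|---|---|---|
| Mortality (Outcome variables, Secondary) | Deaths by arm, with no adverse event record | No, fatal events only |
| Patient and assessor questionnaire (Exploratory outcomes and endpoints) | Sleep disturbance, distraction or discomfort, shock sensation, redness and skin issues | No, tolerability and skin |
| Documented pauses and non-use (device section) | An indirect signal that the device was off | No, not an event record |
| Adverse event form | Skin irritation and allergy | No, excluded by rule |

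5. **Does this fit the DSMB remit?** The board receives the trial's data and is asked to look at safety in general. By step 4, none of these sources carries the events in question. The remit is therefore wider than the data meant to serve it.

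**The case against.** The strongest defence is that targeted safety collection is a stated, reasoned choice in a trial that every site's IRB has approved. The device is local, phase I work is described as showing safety, and the exclusions already lower the risk. The article also commits to ICH-GCP and applicable law. The full protocol and the case report form are not shown, so a separate route for serious device events may exist. Much of this stands: general inpatient events need not be collected, and the gap is established only for the article's wording. It does not remove the point, because the article states a rule with no exception, and excluding high-risk patients at entry does not record events that arise later.

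A reader might infer several stronger things that the article does not support:

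- **That the five questionnaire items contradict the adverse event rule.** They belong to a separate instrument with its own summary. Calling that summary the safety assessment is at most a wording matter.
- **That patients with pacing wires are knowingly exposed to 100 mA.** Their entry is conditional on pacing status, and 100 mA is a ceiling: intensity is raised only until contraction is visible.
- **That all the exclusions prove foreseen electrical, muscle and mechanical harm, or that these are the likeliest harms.** Only fracture displacement is tied to the device, and nothing in the article ranks harms by likelihood.
- **That the DSMB sees no safety data beyond skin.** It sees deaths, questionnaire results and documented pauses.
- **That the defect can be expressed as a rate.** With 274 patients in the stimulation arm and no events observed, the rule of three gives an upper 95% limit of 3/274 = 1.1%. That describes what a trial of this size could say if events were collected. It does not measure the defect.

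**Conclusion.** The point holds in a limited form. As worded, the adverse event section gives no route for recording serious non-skin events, even those attributed to the device. That sits badly with an eligibility criterion that names such a harm and with a DSMB remit that covers safety in general. The other data reaching the board do not fill the gap for non-fatal events.

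The size is one of scope and cannot be quantified from the article. The primary analysis and its error rates are unaffected. What is weakened is the board's safety review and any safety conclusion beyond skin effects, tolerability and mortality. The change should be made, but it is not a reason to doubt the efficacy inference.

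The conclusion assumes that the full protocol and case report form follow the article's rule. If they already provide a route for serious device events, the article's sentence is wrong and only needs correcting.

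**What to change.** Amend the adverse event section in two parts:

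- **(a) Both arms, identically:** collect a short prespecified list of non-skin hazards drawn from the plan's own exclusion criteria. Fracture displacement is the one expressly named. Whether to add cardiac-device or rhythm events and rhabdomyolysis, and how to define them, is for the sponsor and investigators. This list can be compared between arms.
- **(b) Stimulation arm only:** record any serious event the investigator attributes to the device, and report it descriptively. It cannot support a between-arm comparison, because control patients have no device to which an event could be attributed and the trial is open label.

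Submit both to the DSMB at each planned look, and limit any safety conclusion to what was collected. State in the same amendment how the questionnaire's side effects relate to formal adverse events, so that the two are not confused.

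The cost is a few fields on the existing adverse event form, modest site workload and a protocol amendment. General inpatient events stay uncollected, which respects the plan's workload argument. At the end of December 2023 the article reports 176 patients recruited against a minimum of 548. An amendment then would still have covered at least 548 − 176 = 372 patients, or 372/548 = 68% of that minimum. For patients already completed, the report should say that these events were not collected.

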### Frequency and plan for monitoring trial conduct

Monitoring of the trial conduct will be conducted to minimize the number of errors and missing data and, consequently, to generate an accurate database for analysis. Two independent monitors are installed by the sponsor to perform study monitoring. Remote monitoring will be performed to signal early aberrant patterns, issues with consistency, credibility, and other anomalies. On-site monitoring will be conducted by the sponsor in all sites after the first and the third interim analyses to control the presence and completeness of the research dossier and the informed consent forms. Source data checks will be performed in the files of 25% of the patients after completion of the trial.

## Ethical considerations

This trial is conducted in compliance with the protocol, the Declaration of Helsinki, the International Consensus on Harmonization—Good Clinical Practice (ICH-GCP), and all applicable laws and regulations of the countries in which the study is performed. Before sites start recruiting patients, the local investigators must have written and dated approval/favorable opinion from the Institutional Review Board/Independent Ethics Committee (IRB/IEC) for the protocol, consent form, subject recruitment materials/process, and, where applicable, approval by the participating countries competent authority (CA) in accordance with local laws and regulations (Additional file 6). Amendments to the protocol also require IRB/IEC and/or CA approval, where applicable and relevant changes are made to the ClinicalTrials.gov website. All data are stored on a central encrypted, high-security computer system and kept strictly confidential.

## Dissemination

Our dissemination plan includes presentation at national and international conferences and publications in peer reviewed high-impact journals.

## Discussion

Pressure ulcers are associated with high national healthcare costs [3] (3) and are associated with an increased mortality [16]. Despite many preventative measures that have been developed with varying success, few treatments apart from routine wound care practices have been developed. With its mechanisms of increasing local blood flow and redistributing pressure away from muscle-bone interfaces, IES has the potential to facilitate healing and retard progression of pressure injuries. The mechanism would also have significant physiologic plausibility for the prevention of pressure ulcers in high-risk patients, but given the relatively low incidence of pressure ulcers in our analysis, the number of patients required in a trial attempting to demonstrate whether the device can prevent pressure ulcers was prohibitive. Given the burden of pressure ulcers on hospital systems, evaluating the device’s utility for acute care hospital-based treatment of new or established pressure ulcers is necessary.

The device used for this trial has been used in animal trials and small human trials evaluating its efficacy. We opted for testing the impact of electrodes placed around the pressure ulcer overlying the gluteus maximus muscle given its being a large muscle group with the potential to recruit increased blood flow to the area around the ulcer. The specific settings used in terms of frequency and amperage range were initially determined by preclinical data and were also used in the animal and human studies conducted before PROTECT-2.

Limitations for the interpretation of the results of this study do exist. Besides electrical stimulation of the gluteal muscles, other factors may have effect on the progression and healing of ulcers including contemporary wound care treatments, different national standards of treatment, different hospital protocols, and differences between ICU and non-ICU care. However, these findings will not bias the findings of the study given the multicentered, international nature of the trial, and testing for interaction for ICU vs. non-ICU enrollment will be done. In addition, combining stage 1 and stage 2 ulcers for the primary analysis will not enable us to assess whether the IES device may be more effective for 1 stage of ulcer versus stage 2. Nevertheless, in secondary analyses, we will test the interaction, although underpowered, between treatment and baseline stage as well as report the effect for each stage separately.

Much attention has been paid to safety in the PROTECT-2 trial. Accordingly, data and patient safety during the trial is closely monitored by a DSMB, whose members have been chosen due to their expertise in clinical research. The research electronic data capture will be used for building the database within a secure system and allowing access to the eCRF as well as randomization of patients into groups within one single platform for participation sites. Importantly, data on side effects as well as patient and caregiver perceptions of skin health and sleep hygiene will be collected and used to enhance the description of the stimulation device.

In summary, the PROTECT-2 trial is designed to establish the efficacy of IES for treatment of stage 1–2 sacral and ischial pressure injuries in hospitalized patients.

## Trial progress

This paper is based on the most recent version of the study protocol (i.e., v5.0, 2023-12-29). The first patient was randomized on June 6, 2022. As of December 30, 2023, we have recruited 176 patients across 3 centers in 2 countries. The first interim analysis based on recruitment is anticipated to be completed January 2024.

## Data Availability

All institutions and investigators participating in the trial will have access to the final dataset and will be able to freely publish and disseminate study results. The datasets analyzed during the current study and statistical code are available from the corresponding author on reasonable request, as is the full protocol.

## Abbreviations

CA: Competent authority
CTCAE: International Common Terminology Criteria for Adverse Events
CRF: Case report form
DSMB: Data and safety monitoring board
GEE: Generalized estimating equation
IRB/IEC: Institutional review board/independent ethics committee
ICC: Intraclass correlation
ICERS: Incremental cost-effectiveness ratios
ICH-GCP: International Consensus on Harmonization – Good Clinical Practice
IES: Intermittent electrical stimulation
LAR: Legally authorized representative
PH: Proportional hazard
